## Abstract

**Background:**

Chronic pain conditions are complex multifactorial disorders with physical, psychological, and environmental factors contributing to their onset and persistence. Among these conditions, the role of brain-derived neurotrophic factor (BDNF) and the impact of a specific therapeutic education (TE) on pain management have emerged as important areas of research.

**Objective:**

This study aims to investigate the effects of a specific type of therapeutic education on pain levels and BDNF concentrations.

**Methods:**

In this single-blind, randomized clinical trial, patients will be randomly assigned to one of two groups: one will receive exercise with TE and the other without TE. Assessments will be made at baseline, mid-treatment, post-intervention, and at one and eight months.

**Outcomes:**

This study will shed light on the effectiveness of a therapeutic education (TE) program in pain management. Additionally, it will provide information on its effects on BDNF levels, a biomarker of brain plasticity, as well as on various psychosocial variables that can influence pain experience.

**Conclusion:**

By comprehensively addressing the need to quantify brain changes more precisely in individuals with chronic pain during interventions like TE and recognizing the importance of establishing a more structured and comprehensive protocol, this study lays a solid and replicable foundation for future evidence-based treatment developments.

## Background

Chronic pain is a widely prevalent health problem that affects one in five people worldwide [1]. It is a debilitating condition with a potentially significant impact on one’s quality of life, affecting one’s ability to perform daily activities and decreasing one’s emotional and physical well-being [2], as well as the resources needed to cope therewith [3]. One serious drawback that accompanies chronic pain is the frequent dependence on drugs for pain relief. In particular, opioids have become one of the main medications for treating pain, as also one of the causes of the increase in mortality due to overdose [4] However, physiotherapy modalities that include therapeutic education and exercise are a common non-pharmacological therapeutic approach for chronic pain and its maladaptive plasticity [5–7], defined as a change in the structure or function of the nervous system resulting in increased pain sensitization [8, 9]. Specifically, therapeutic education (TE) plays a crucial role in reversing maladaptive plasticity, reducing pain and disability, fear avoidance, and pain catastrophizing, *inter alia* [10] TE is a fundamental component of chronic pain management and addresses several aspects essential for improving patients’ quality of life [11, 12]. These include understanding pain and its mechanism of production [13], promoting self-regulation and self-care strategies [14], acquiring coping skills [15], reducing fear-avoidance and pain catastrophizing [16], promoting healthy lifestyles, and optimizing physical functionality [17]. One of the main goals for the patient is to reconfigure maladaptive beliefs associated with their chronic pain, involving a change in the structure and function of the nervous system that has contributed to increased pain sensitization [18, 19].

However, no random educational approach is appropriate for this. There are several types of TE, addressing different topics [20, 21] and using different dosages [22–24], which inevitably lead to different results [25–27]. A specific approach is required that considers both the biological and behavioral aspects of chronic pain. Further, to accurately determine the true impact of such non-only-informative intervention, it is imperative to measure and evaluate the effects of the TE not only in terms of perceived pain and psychosocial factors but also through the lens of brain plasticity biomarkers and draw correlations within these domains.

In this sense, biological components like brain-derived neurotrophic factor (BDNF) and its relationship to cerebral plasticity in patients with persistent pain [28, 29]. BDNF, a protein that plays an important role in pain sensitization and neuronal plasticity, has been associated with neuronal hyperexcitability in chronic pain [30]. Understanding its relationship to pain is crucial for developing new therapies. Manipulating BDNF expression could offer options for modulating neuronal plasticity and relieving pain in patients with chronic pain. However, the impact of these interventions on the adaptive changes in the brain, which are crucial in patients with persistent pain, remains largely unknown. Additionally, a lack of adherence to established guidelines for reporting interventions, such as the TIDieR checklist for general interventions [31], or GREET checklist for educational interventions [32] and the Consensus on Exercise Reporting Template (CERT) checklist for exercise interventions [33] hinders their replication and adaptation to individual patients, thus limiting their practical utility [34].

In summary, despite the challenges in the field of education and exercise for chronic pain management, this model of pain TE will address the aforesaid needs, providing a comprehensive and evidence-based approach that considers changes in brain plasticity learning-related, biobehavioral aspects, appropriate dosing, and objective evaluation of results.

## Materials and methods

### Study setting

The proposed study is a single-blind, parallel-group, randomized control trial. Its protocol follows the structure based on the PICO question (Population, Intervention, Comparison, Outcome) [35] and adheres to the recommendations of the Standard Protocol Items: Recommendations for Interventional Trials (SPIRIT) guideline [36]. In addition, specific interventions were described based on the Template for Intervention Description and Replication (TIDieR) checklist [31], the Guideline for Reporting Evidence-based Practice Educational Interventions and Teaching (GREET) [32], and the Consensus on Exercise Reporting Template (CERT) checklist [33]. The trial was approved by the ethics committee of Rey Juan Carlos University (Ethical number: 1901202202822) and the entire study will be conducted at the Universidad Rey Juan Carlos located in Alcorcón, Madrid (Spain). The trial identifier code is NCT05623579, registered on November 18, 2022, in ClinicalTrials.gov.

### Eligibility criteria

Patients will be recruited from the physical therapy clinics located in Madrid, Spain, based on the following inclusion criteria: aged between 18 and 65, having a history of pain lasting more than twelve weeks, pain corresponding to at least 3 out of 10 on the visual analog scale, possessing the ability to comprehend, speak, and write in Spanish, not currently undergoing any other treatments for 3 months before the study, and explicitly consenting to not being allowed to initiate new treatments till the end of the follow-up period. The exclusion criteria are neurological cognitive alteration that prevents understanding the contents of the educational program (in case of doubt, assessment with the Mini-Mental test will be conducted, requiring a minimum score of 25), systemic, oncological, or inflammatory diseases, psychiatric pathologies, pregnancy, diabetes type II and inability to adhere to the protocol.

The following professionals were selected to conduct the study: two physiotherapists with more than 15 years of experience in the treatment of chronic pain for the pain education and exercise therapy component, two nurses for blood collection, another physiotherapist for administering questionnaires on psychosocial variables and quantitative sensory testing, and two biochemists for BDNF analysis.

### Interventions

All patients who meet the inclusion criteria and agree to participate in the study will be informed verbally and in writing, with the delivery of the information sheet listing the specific characteristics of the study. They will be asked to sign the written informed consent form.

Sociodemographic data will then be collected, as well as psychosocial variables on their current pain process. This data collection will be carried out in a room in the physiotherapy gymnasium of the university center, previously designated for measurements by the evaluating researcher as well as blood extraction.

Once the specific questionnaires and the pressure pain threshold (PPT) at the joints of the elbow and tibialis anterior are measured, a trained professional will collect 5 ml of blood from the ulnar vein of the participants in a citrate vacutainer. The blood collection will always take place between 6 p.m. and 7 p.m., to minimize the possible effects of circadian changes [37–39]. Blood samples will be collected in tubes containing K3-EDTA and centrifuged at 1000 g for 10 min at 4°C. The supernatants for the total plasma (TP) condition will be frozen at -80°C. Blood collection will be performed in both groups at rest before the intervention, 15 days after the intervention, at the end of the intervention period, and at 1 month and 8 months after the intervention.

After the initial data collection, a researcher other than the initial evaluator, and the physiotherapist-therapist who will apply the subsequent treatment to ensure blinding, will proceed to randomly assign the subjects to one of the two study groups through a list previously generated with GraphPad software (version 5.01 Graphpad software, Inc. San Diego, California, USA).

### Intervention group (Exercise + POBTE)

Patients assigned to the intervention group will be instructed by a physiotherapist in the performance of the TE sessions according to their functional capacity, with reference to their HRmax [40]. They will be prescribed the reference intensity measures for the expected increase in training time indications on potential risks and references for the interruption of the exercise in their case. The duration of the exercise program will be 4 weeks, with 3 sessions lasting a maximum of 45 minutes per session. On alternate days, twice a week, the patient will receive *Pain Oriented Biobehavioral Therapeutic Education (POBTE)* sessions, focusing on the specific parameters described below. The duration of the sessions will be a maximum of 45 minutes each day [41], and the education program will be spread across 8 sessions over 4 weeks. The intervention group will be instructed to refrain from discussing treatment details with participants assigned to the control group until the end of the treatment and follow-up periods.

The main learning areas that to be addressed and the biobehavioral interventions proposed are summarized in Fig 1, and the conceptual framework of the POBTE intervention is explained in detail in Fig 2 and S1 File. The specific cognitive components of the intervention are listed in the general intervention checklist, following the TiDier checklist (see S1 Checklist) and the exercise intervention is presented in S2 Checklist with the CERT checklist, while the Therapeutic Educational Intervention is presented in S3 Checklist with the GREET checklist.

**Fig 1 pone.0289430.g001:**
[figure not shown]
POBTE’s strategies.

**Fig 2 pone.0289430.g002:**
[figure not shown]
POBTE’s intervention.

A chronological representation of the tasks to be performed during the POBTE intervention is displayed in Fig 2. This figure is arranged to correspond to the stages of the meaningful learning phase in the intervention design.

### Active control group (Exercise)

Patients assigned to the active control group will be instructed by a physiotherapist in the performance of TE sessions according to their functional capacity, with reference to their HRmax. They will be prescribed the reference intensity measures for the expected increase in training time, indications of potential risks, and references for the interruption of the exercise in their case. The duration of the exercise program will be 4 weeks, with 3 sessions lasting a maximum of 45 minutes per session. Contents of the exercise intervention are described in the CERT checklist (S2 Checklist).

### Intervention modifications

The criteria for discontinuing or modifying allocated interventions for a given trial participant would include participant request, adverse events, or harms, improvement in or worsening of the disease, and non-compliance. In the context of this study, criteria will be adapted to the specific needs and characteristics of the study population.

### Intervention adherence

To improve adherence, we will provide clear instructions, personalized feedback, and support, simplify the intervention as much as possible without losing scientific rigor, and monitor attendance, self-reports, and reminders. Written materials and videos will be provided, along with personalized feedback, progress reports, and regular check-ins. Attendance, self-reports, and reminders will be used to monitor adherence.

## Outcomes

### Primary outcome

#### Pain intensity

*Visual Analogue Scale (VAS)*. Pain intensity will be measured using a 100 mm visual analog scale where 0 represents ‘no pain’ and 100 the ‘worst pain imaginable’. Participants draw a mark at a point on the line that best reflects the pain they are experiencing at the time of measurement. Higher scores indicate higher pain levels. The sensitivity and specificity of this questionnaire and the acceptability of its psychometric properties have been approved [42].

### Secondary outcomes

#### Biochemical

*Plasma BDNF levels*. Within 30 minutes of collection, the blood samples will be centrifuged and the plasma separated into 0.5 ml aliquots for further analysis. Plasma BDNF levels will be determined by enzyme-linked immunosorbent assay (ELISA) test using monoclonal antibodies specific to neurotrophin (R&D Systems, Minneapolis, MN), using the manufacturer’s protocol. All samples will be tested in duplicate to avoid intra-assay variations. The lower limit of detection for BDNF from the kit is 7.8 pg/mL. Assay (ELISA) will use a ChemiKine BDNF ELISA kit, CYT306 (Chemicon/Millipore, Billerica, MA). Optical density will be measured using an ELISA reader at a wavelength of 450 nm (GloMax-Multi Microplate Reader, Promega, Madison, WI) for multiplex assay measurements. Data will be expressed in pg/mg protein.

#### Psychosocial

*Anxiety and depression* will be assessed using the Spanish-validated version of the HADS self-completion scale. This scale is divided into two subscales of 7 items each: 1) depression (HADSDep) and 2) anxiety (HADSAnx). The HADS has demonstrated good reliability and validity in various pathologies [43].

*Quality of life*. Measured with the EuroQoL-5D questionnaire (EQ-5D), this is a self-report instrument to assess the health-related quality of life comprised of three items, a 5-factor descriptive scale, a second item comprising a vertical VAS and a third one about social values index generated by the instrument. The EQ-5D has shown good psychometric characteristics [44].

*Catastrophism* will be measured by the Spanish version of the Pain Catastrophism Scale (ECD). This has demonstrated adequate psychometric characteristics for the assessment of this construct with internal validity (Cronbach’s alpha 0.81) [45].

*Chronic Pain Grading Scale (CPGS)* is a self-report instrument consisting of an 8-item scale. It has a high internal consistency, with a Cronbach’s α of 0.87, similar to that of other language versions, and an intraclass correlation coefficient of 0.81. The average administration time is 2 min 28 s [46].

*Tampa Scale for Kinesiophobia (TSK)* is a self-report questionnaire comprising 17 items. The internal consistency of the TSK is high, with Cronbach’s alpha coefficients ranging from 0.74 to 0.93, indicating strong reliability. Test-retest reliability is also good, with correlation coefficients ranging from 0.75 to 0.88 [47].

*Pittsburgh Sleep Quality Index (PSQI)* is a self-rated questionnaire of 19 items categorized into seven components, viz., subjective sleep quality, sleep latency, sleep duration, habitual sleep efficiency, sleep disturbances, use of sleep medication, and daytime dysfunction. The internal consistency of the PSQI is high, with Cronbach’s alpha coefficients ranging from 0.77 to 0.83, indicating strong reliability. Test-retest reliability is also good, with correlation coefficients ranging from 0.85 to 0.87 [48].

*Perceived Stress Scale* is a self-report questionnaire comprising 10 items, each rated on a 5-point Likert scale ranging from 0 (never) to 4 (very often). The internal consistency of the PSS is high, with Cronbach’s alpha coefficients ranging from 0.78 to 0.91, indicating strong reliability. Test-retest reliability is also good, with correlation coefficients ranging from 0.67 to 0.85 [49].

*International Physical Activity Questionnaire (IPAQ)* is a self-reported questionnaire of 27 items to assess the frequency, duration, and intensity of physical activity. The internal consistency of the IPAQ is moderate to high, with Cronbach’s alpha coefficients ranging from 0.73 to 0.95. Test-retest reliability is good, with correlation coefficients ranging from 0.70 to 0.88 [50].

*Chronic Pain Self-Efficacy Scale (CPSS)* is a self-reported questionnaire comprising 22 items rated on a 0–10 scale, with higher scores indicating greater self-efficacy in managing pain. The internal consistency of the CPSS is high, with Cronbach’s alpha coefficients ranging from 0.89 to 0.95, indicating strong reliability. Test-retest reliability is also good, with correlation coefficients ranging from 0.63 to 0.90 [51].

*Knowledge questionnaire on specific aspects of pain*, *ad hoc*, includes 5 questions in multi-choice test format on the contents used in the education sessions.

*Global Perception of Change is* the only one that will be tested after the intervention. This instrument consists of a 100mm line numbered in centimeters from -5 to 5 where the left end reads "Much Worse", 0 is printed as "no change" and 5 is marked as "fully recovered". Relative to these values, the patient is asked to answer the following question: "In relation to your pain, how would you describe your current state of health compared to when your pain began?" This version of the change perception scale has been assessed in the literature as the most appropriate in musculoskeletal pain processes, and as a valid and reliable instrument [52].

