#### Others

*Pressure Pain Thresholds (PPT)*. Pressure pain thresholds will be assessed through a pressure algometer. The algometer will be applied to different points in the body (elbow and knee) and participants will be asked to indicate the point at which pressure changes to pain. The pressure will be gradually increased at approximately 1 kg/s until the participant indicates feeling pain. The threshold pressure at which the sensation changes from pressure to pain will be recorded in kilograms (kg) and used as an indicator of PPT. Higher PPT values indicate higher pain thresholds. The validity and reliability of using a pressure algometer to measure PPT have been established [53].

*Height and weight*. Both these variables will be determined by patient estimation, with no exploration of them in the measurement process.

*Sociodemographic*. This comprises Age, Marital status (Single, Married, Divorced, Widowed), Employment status (Active, Unemployed, Retired, Temporary disability, Student, Homemaker, Other), Educational level (none, primary, secondary, university), and Gender.

*Exercise*. Among the exercise variables, the parameters described below will be considered:

*Blood pressure and respiratory rate*. Measured with the Anura application, which has demonstrated reliability with a conventional blood pressure measurement of 98% [54].

*Saturation and HR* are Measured with an Oxylink finger pulse oximeter.

All the outcome measurements will be assessed in a random order at baseline, at the halfway point of the treatment, post-intervention, and one- and eight-months post-intervention (Figs 3–5).

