### Blinding

#### Masking

In this trial, both outcome assessors and data analysts will be blinded after intervention assignment. They will not know the participants’ intervention group affiliations during outcome assessment or data analysis. Due to the intervention’s nature, involving educational sessions and exercises requiring interaction, participants and educators cannot be blinded.

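### Assessor blinding for pressure pain thresholds is at risk and unprotected, because the same physiotherapist administers, in random order, a knowledge test on content taught to only one arm

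*Protocol article*

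**What the plan says.** - **Staff (Eligibility criteria).** After the two treating physiotherapists and the nurses, the list names "another physiotherapist for administering questionnaires on psychosocial variables and quantitative sensory testing". One role covers both tasks.
- **Knowledge test (Secondary outcomes, Psychosocial).** This ad hoc questionnaire "includes 5 questions in multi-choice test format on the contents used in the education sessions".
- **Who is taught (Intervention group; Active control group).** The education programme of 8 sessions over 4 weeks goes to the intervention arm only. The control arm receives exercise alone.
- **Order and timing (Secondary outcomes, Others).** "All the outcome measurements will be assessed in a random order at baseline, at the halfway point of the treatment, post-intervention", and again one and eight months afterwards.
- **PPT (Others).** An algometer is applied at the elbow and knee. Pressure rises at about 1 kg/s until the participant reports pain, and the value is recorded.
- **Blinding (Masking).** "both outcome assessors and data analysts will be blinded after intervention assignment", and "They will not know the participants’ intervention group affiliations during outcome assessment or data analysis". By contrast, "participants and educators cannot be blinded".
- **Disclosure (Intervention group).** The one instruction on this is: "The intervention group will be instructed to refrain from discussing treatment details with participants assigned to the control group". The assessor is not mentioned.

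**The concern.** A test of what one arm was taught is, by design, an indicator of arm, and the better it works, the more it tells. Here it falls to the person who is meant not to know the arm and who also applies the algometer. The random order means that no rule puts PPT first.

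PPT is where assessor blinding has a clinical job to do. The pain scale and most questionnaires are completed by patients who know their arm, so blinding the assessor cannot protect them. BDNF is analysed by separate biochemists. For PPT, the assessor controls the rate of force, any prompting and the recording of the value. An assessor who suspects the arm could shift these without meaning to, and no analysis can restore blinding afterwards.

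**Working it through.** The plan gives no figure on this point, and the sample size (66 per group) does not depend on it. The check has two parts.

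**1. Is the route open as written?**

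- One physiotherapist has both tasks: stated.
- That physiotherapist handles the knowledge test: inferred, because it is listed under Psychosocial and the role covers psychosocial questionnaires.
- The content is taught to one arm only: stated.
- The knowledge test can precede PPT: follows from the random order of all outcomes.
- The assessor reads or scores the answers: not stated. The response mode of this test is not given.

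If any order of two items is equally likely, the knowledge test comes before PPT in about half of sessions. That limits exposure only at the first post-baseline visit, the halfway point. If the same physiotherapist does every visit, the remaining three PPT sessions (post-intervention, one month, eight months) all follow at least one post-baseline knowledge test, whatever the order on the day.

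**2. How informative would a seen score be?**

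The document gives no success rates, so the following are assumptions: five independent items, a common probability correct of p_E in the education arm and p_C in the control arm, 1:1 allocation (from the Sample size section), and an assessor who sees the total and makes the best guess. Then

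accuracy = 0.5 × Σ max[Bin(x; 5, p_C), Bin(x; 5, p_E)], for x = 0 to 5.

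For the pairs below, the best guess is education when 4 or more items are correct, so

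accuracy = 0.5 × [P(X ≥ 4 | p_E) + P(X ≤ 3 | p_C)].

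Worked example, p_E = 0.80 and p_C = 0.40:

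- P(X ≥ 4 | 0.80) = 5 × 0.80⁴ × 0.20 + 0.80⁵ = 0.4096 + 0.3277 = 0.7373
- P(X ≤ 3 | 0.40) = 1 − (5 × 0.40⁴ × 0.60 + 0.40⁵) = 1 − (0.0768 + 0.0102) = 0.9130
- accuracy = 0.5 × (0.7373 + 0.9130) = 0.825

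| p_C | p_E | Correct guesses |
|---|---|---|
| 0.60 | 0.70 | 60% |
| 0.50 | 0.70 | 67% |
| 0.60 | 0.80 | 70% |
| 0.50 | 0.80 | 78% |
| 0.40 | 0.80 | 83% |
| 0.30 | 0.90 | 94% |
| 0.25 | 0.90 | 95% |

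Chance is 50%. These figures are for a single score. Repeat visits, and comparison with the baseline score, could add information. Control patients becoming familiar with the items, and a halfway visit at which only part of the programme has been given, would reduce it. None of these is quantified here.

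**The case against.** The strongest reply is that the decisive step is not in the document. Administering a questionnaire may mean no more than handing over a form. Most neighbouring instruments are described as self-report, and a multiple-choice test suits that mode. The accuracies rest on assumed success rates, and the lowest, 60%, is not far from chance. The measure at stake is a single secondary outcome with a specified rate of force, and its endpoint is signalled by the patient, who is unblinded anyway. Form handling is also the kind of detail that a journal article leaves to the full protocol.

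Much of this stands. A reader might infer that the test answers disclose the arm, so that the Masking statement is false and the single-blind description fails. The document does not support that. It does not say that the assessor sees the answers, and five answers give a probability rather than an identification, since control patients can answer correctly too. The patient's own lack of blinding also limits how much assessor blinding can protect PPT.

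Two things do not fall away. First, the point does not rest on omission alone: the staffing and the random order are both stated, and together they open the route. A rule elsewhere that put the knowledge test last would contradict the statement that all outcomes are taken in random order. Second, although the patient signals the endpoint, the assessor still controls rate, prompting and recording.

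**Conclusion.** The concern holds as a risk, not as a demonstrated loss of blinding. As written, the arrangements give the PPT assessor a route to information about the arm, and the article describes nothing that closes it.

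If the assessor sees the answers, one score would allow roughly 60% to 95% correct guesses, against 50% by chance, and the knowledge can persist to later visits. This depends on three assumptions: that this physiotherapist handles this form (inferred from its heading), that the answers are seen, and that success rates lie in the range shown. The resulting bias in PPT cannot be sized from the document.

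The primary pain scale is marked by the patient and is not affected by this route. The point deserves correction because PPT is the clinical measure that assessor blinding can protect and the remedy costs almost nothing.

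**What to change.** - Take the knowledge questionnaire out of the random order. The patient completes it alone, as the last item of each visit, after PPT.
- The patient returns it in a sealed envelope that the assessor neither opens nor scores.
- Extend the non-disclosure instruction in the Intervention group section so that patients in both arms are asked not to mention treatment content to the assessor.

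The cost is a few sentences of protocol text, a small change to the visit procedure and a supply of envelopes. The sample size and the analysis are unchanged. The one small downside is that this item no longer takes part in the random order. The change has to be in place before the post-baseline visits to be of use.
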